# 3-dimensional versus conventional laparoscopy for benign hysterectomy: protocol for a randomized clinical trial

**DOI:** 10.1186/s12905-017-0434-7

**Published:** 2017-09-07

**Keywords:** Conventional laparoscopy, 3-dimensional laparoscopy, Hysterectomy, Daily living, Postoperative pain

## Abstract

**Background:**

Hysterectomy is one of the most common surgical procedures for women of reproductive age. Laparoscopy was introduced in the 1990es and is today one of the recommended routes of surgery. A recent observational study showed that operative time for hysterectomy was significantly lower for 3-dimensional compared to conventional laparoscopy. Complication rates were similar for the two groups. No other observational studies or randomized clinical trials have compared 3-dimensional to conventional laparoscopy in patients undergoing total hysterectomy for benign disease.

The objective of the study is to determine if 3D laparoscopy gives better quality of life, less postoperative pain, less per- and postoperative complications, shorter operative time, or a shorter stay in hospital and a faster return to work or normal life, compared to conventional laparoscopy for benign hysterectomy.

**Methods/design:**

The design is a randomised multicentre clinical trial. Participants will be 400 women referred for laparoscopic hysterectomy for benign indications. Patients will be randomized to 3-dimensional or conventional laparoscopic hysterectomy. Operative procedures will follow the same principles and the same standard whether the surgeon’s vision is 3-dimensional or conventional laparoscopy. Primary outcomes will be the impact of surgery on quality of life, assessed by the SF 36 questionnaire, and postoperative pain, assessed by a Visual Analogue scale for pain measurement. With a standard deviation of 12 points on SF 36 questionnaire, a risk of type I error of 3.3% and a risk of type II error of 10% a sample size of 190 patients in each arm of the trial is needed. Secondarily, we will investigate operative time, time to return to work, length of hospital stay, and - and postoperative complications.

**Discussion:**

This trial will be the first randomized clinical trial investigating the potential clinical benefits and harms of 3-dimensional compared to conventional laparoscopy. The results may provide more evidence regarding the future place of 3-dimensional laparoscopy in the range of endoscopic approaches for benign hysterectomy.

**Trial registration:**

This study is registered at ClinicalTrial.gov: NCT02610985 November 16th 2015. November 2015. The regional Ethical committee approved it on the 12. November 2015, approval number: SJ-498. Data handling was approved by the Danish Data Protection Agency: REG-109-2015 on the 13. November 2015.

## Background

Today it is generally accepted that the procedures of choice for the removal of uterus on benign indication should be laparoscopic or vaginal surgery. Both procedures are associated with shorter hospital stay and faster recovery compared to laparotomy [1–4]. Vaginal hysterectomy has lower costs and in some studies, a lower complication rate compared to laparoscopy [5]. In younger women without prolapse, however, the operation is not as straightforward as in older women. Furthermore, proper access to the pelvic cavity is not provided by the vaginal route, which makes laparoscopy first choice when the procedure involves adnexal surgery. In many departments, adnexal surgery has become part of the standard procedure for hysterectomy, since recent studies suggest that concomitant removal of the fallopian tubes may decrease the risk of development of ovarian and peritoneal cancer [6].

Despite promising results, adoption of the laparoscopic approach for benign hysterectomy has been slow. A longer operating procedure, the requirement of advanced laparoscopic skills, and challenges in especially obese patients have been cited as the main reasons [7]. Accordingly even today only a minor proportion of all benign hysterectomies are performed laparoscopically in European countries.

In 2005 the US Food and Drug Administration approved the Da Vinci robotic platform for gynaecologic surgery. Due to improved dexterity, ergonomics, and a 3-dimensional imaging the technology was promoted to overcome many of the limitations and drawbacks of conventional laparoscopy [8]. Within few years, the number of benign hysterectomies performed by robotic-assisted laparoscopy showed a tremendous rise. Benefits compared to conventional laparoscopy, however, have not been reported [9]. On the contrary, a randomized trial concludes that robotic assistance may lengthen operative time for benign hysterectomy with an average of 77 min compared to conventional laparoscopy [10].

Three-dimensional (3D) laparoscopy offers the same 3-dimensional stereoscopic imaging as robotic surgery, but in a conventional laparoscopic set-up with much lower costs [11]. Although dexterity and ergonomics are theoretically inferior to those of robotic surgery, docking of the big and inconvenient patient robotic-cart is avoided, reducing the number of operative steps. Furthermore, instruments are held by the surgeon and not by robotic arms, which means a preservation of the tactile sense. The place of 3D laparoscopy in the range of endoscopic approaches for benign hysterectomy, however, is not clear. An updated literature search in PubMed and Embase, using Mesh terms and the search string *““Imaging, Three-Dimensional”” [Mesh]) AND ((““Hysterectomy”” [Mesh]) OR laparoscopic hysterectomy) (19–02-2015)*, demonstrates that data are sparse. No randomized trials exist, and only a single retrospective study has been published within gynaecological surgery. In that study, operative time for hysterectomy was significantly lower for 3D compared to conventional laparoscopy. Complication rates were similar for the two groups [12].

In conclusion, although laparoscopy is one of the recommended routes of surgery for benign hysterectomy, the place of 3D laparoscopy in the range of endoscopic approaches is not clear. Robotic surgery for hysterectomy was introduced without evidence for the clinical benefit, underlining the importance of clinical trials before implementation of new techniques. We expect that 3D- technology improves imaging and facilitates faster and safer surgery, causing less pain, shorter recovery and fewer postoperative complications.

## Methods and design

### Aim

The objective of the study is to determine if 3D laparoscopy gives better quality of life, less postoperative pain, less per- and postoperative complications, shorter operative time, or a shorter stay in hospital and a faster return to work or normal life, compared to conventional laparoscopy for benign hysterectomy.

### Design

An investigator-initiated, blinded, randomized, clinical trial.

### Setting

Roskilde University Hospital, Denmark.

Herlev University Hospital, Denmark.

### Participants

Participants will be patients referred for laparoscopic hysterectomy with or without bilateral salpingectomy or bilateral salpingo-oophorectomy for benign indications. Women not suitable for laparoscopic hysterectomy, either because of [1] ultrasound appraisal of uterus weight > 1000 g or [2] decision to carry out concomitant prolapse surgery, will not be included. Further, patients not able to read and understand Danish or give informed consent are also excluded (Fig 1).

**Fig. 1 Fig1:**
[figure not shown]
Participant flowchart in accordance with the CONSORT statement

### Interventions

In order to assess which mode of laparoscopy is more favourable in a RCT, it is necessary to use similar and well-defined procedures in all other areas around the surgery. Therefore the preoperative information and patient education is standardized. Pre-emptive medication is 8 mg dexamethasone, 2 g paracetamol, 400 mg Ibumetin and 4 mg Ondacetron. Anaesthesia and postoperative care is also standardized as well as the operative procedure.

Standard preoperative assessment will be performed together with transvaginal ultrasound estimating the size of the uterus. Operative procedures will follow the previously described “Gold standard” as follows: A manipulator will be used in all patients to expose and delineate different anatomical structures. For ligation and dissection, a Thunderbeat® bipolar/ultrasound sealing and cutting energy device will be used. After detachment, uterus will be removed through the vaginal vault. In case of a very narrow vagina combined with a myomatous uterus it may be necessary to enlarge the abdominal incision [13]. Morcellation or any other destruction of the uterus inside the abdomen will not be performed. The vaginal vault will be closed laparoscopically with a running Vicryl 2–0 suture or a barbed suture V-lock® 2–0. Urinary catheter will be removed immediately after the operation. For postoperative pain relief, the patients will be given sufentanil/Fentanyl in the recovery ward, and paracetamol, NSAID and in some cases morphine in the gynaecological unit. After a few hours on the recovery ward, they will return to the gynaecological unit.

### Data collection

Patients found suitable for participation will be informed about the trial. If the patient wants to participate she will fill out a quality of life questionnaire (SF 36-v2).

*If willing to participate, and after instructions on how to understand the questionnaire the patient completes the SF-36 questionnaire in the preoperative assessment. To reduce risk of bias at the 6 week postoperative telephone interview, patient is re-introduced to and provided with a copy of the SF 36 questionnaire at the time of discharge; further, the research nurse is instructed to stay neutral at the telephone interview* Randomization will be performed in the morning of the operation day. A visual analogue-scale (VAS) for pain scoring will be used when the participants return to the gynaecological unit, 5 h postoperatively. Hospital discharge will be considered when the women are fully mobilized, urinating and pain is controlled with milder oral analgesia. At discharge, use of painkillers stronger than over-the-counter medicine will be registered. The women will be asked to scale their pain at a VAS score in the morning of the first 3 days after discharge. Six weeks after surgery, all patients will receive a telephone call from a nurse, where a SF-36-v2 questionnaire similar to that given preoperatively will be filled out. Pre-operative data is registered by the doctor in the outpatient department record sheet, Operative data by the surgeon in the operation record sheet, and Postoperative data recorded by the nurse surgeon in the discharge department record sheet. Any readmission or complications causing readmission is registered by the doctor in the readmission sheet and will be double-cheeked at the telephone interview. If readmitted or treated at another hospital, this will be registered (linked to personal identification number) at the national patient register where all diagnoses are registered and compiled, with the Hysterectomy Database ensuring no complication will be overlooked.

Time to return to work or other normal life, use of postoperative painkillers, and postoperative complications are noted by the nurse in the telephone interview 6 weeks after the operation (Table 1).

**Table 1 Tab1:** Plan for obtaining data for both 2- and 3D hysterectomies

3D and conventional laparoscopic hysterectomy	Enrolment in outpatient clinic	Allocation and operation	Discharge from hospital	Telephone interview
TIMEPOINT	-t1	0	tx	tx + 6 weeks
Baseline variables: height, weight, age, prior operations, chronic pain, parity, estimated weight of uterus, indication for operation, site. Quality of life by SF-36 questionnaire	x	x		
Outcome variables 1: operating time, bleeding, concomitant surgery, weight of uterus		x		
Outcome variables 2: Postoperative pain and medication	x		x	
Outcome variables 3: re-admissions, complications at home, return to work, pain, return to daily living, unexpected malignancy. Quality of life by SF-36 questionnaire	x			x

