### Outcomes

#### Primary outcomes

The impact of surgery on quality of life, assessed by questionnaire (SF-36-v2, physical health score) at a telephone interview 6 weeks postoperatively.
*Postoperative pain is assessed on a 100 mm VAS-scale immediately after the operation at the admission to post anaesthesia care unit (PACU) and again 5 h postoperatively at gynaecological unit or at the PACU if the patient unexpectedly has not returned to gynaecological unit. These measures are related to the patient lying quiet in the bed. Further pain related to physical movements, will be reported in the morning on day 1–3 postoperatively (longitudinal data). Postoperative pain will also be related to the analgesics given as we register the use of units of morphine during the first 3 days.*

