#### Length of hospital stay (hours)

With a sample size of 190 women in each arm of the study, an alpha value of 5% and an average discharge of 48 h postoperatively versus 40 h, and a standard deviation of 25 h, we have a power of 84%.

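### The three morning movement-pain readings, part of the co-primary pain outcome, are timed from discharge in one section and from surgery in another

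*Protocol article*

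**What the plan says.** The pain outcome has two parts.

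- **Resting pain on the day of surgery.** Primary outcomes takes VAS readings "immediately after the operation at the admission to post anaesthesia care unit (PACU) and again 5 h postoperatively at gynaecological unit" (or still in the PACU if the woman has not moved). Both are tied to the operation.
- **Movement pain on three mornings.** Primary outcomes says this "will be reported in the morning on day 1–3 postoperatively (longitudinal data". Data collection says instead: "The women will be asked to scale their pain at a VAS score in the morning of the first 3 days after discharge".

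Other text bears on the difference:

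- Discharge depends partly on pain: "Hospital discharge will be considered when the women are fully mobilized, urinating and pain is controlled with milder oral analgesia".
- The power statement for stay assumes "an average discharge of 48 h postoperatively versus 40 h, and a standard deviation of 25 h, we have a power of 84" per cent. It does not say which arm has which mean, but the Aim looks for 3D to give "or a shorter stay in hospital and a faster return to work or normal life, compared to conventional laparoscopy for benign hysterectomy".
- Next to the postoperative day 1 to 3 readings, Primary outcomes adds: "Postoperative pain will also be related to the analgesics given as we register the use of units of morphine during the first 3 days".
- Statistical analyses assigns longitudinal data to an area-under-the-curve (AUC) summary.

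Table 1 has columns for enrolment, operation, discharge and the six-week interview, but none for individual postoperative days, so it does not settle the matter.

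**The concern.** The two sentences give one set of readings two different starting points. They agree only for a woman who goes home on the day of her operation. This decides which data are collected, so an analysis plan cannot repair it afterwards, and the two centres could each follow a different sentence.

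If the Data collection sentence is the one used, there are three consequences:

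1. The outcome as defined is not collected for most women, because they are still in hospital on the first postoperative morning.
2. The clock for a pain outcome is started by an event after randomisation that itself requires pain to be under control. Women then enter the series at a similar state of recovery whichever arm they are in, which can weaken a true contrast.
3. If stay differs between arms, the AUCs are compared at different times since surgery. The arm discharged earlier is read earlier, when pain is presumably still higher.

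**Working it through.** **Inputs from the article.** Pain: difference 10 mm, SD 20 mm, type I error 3.3%, power 90%, two-sided, 1:1, stated 92 per arm. Trial size: 190 per arm. Stay: 48 h versus 40 h, SD 25 h.

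**Reproducing the plan's figures.**

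- Pain sample size: n = 2 × (2.132 + 1.282)² × (20/10)² = 93.2, so 94 per arm. The stated 92 is within two patients, so the inputs are read correctly.
- Power for stay: SE = 25 × √(2/190) = 2.565 h and 8/2.565 = 3.119. At 5% type I error, Φ(3.119 − 1.960) = 87.7%. At 3.3%, Φ(3.119 − 2.132) = 83.8%. The stated 84% therefore matches the 3.3% level rather than the 5% written there. This does not affect the present point, which uses only the means and the SD.

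**Step 1: when discharge-timed readings would fall.** 40 h is 1.67 days and 48 h is 2.00 days, so the first morning after an average stay is about postoperative day 2 to 3. As an illustration, assume surgery at 10:00, a gamma-distributed stay with the stated means and SD, and a first reading on the calendar day after discharge:

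| Mean stay | Mean day of first reading | First reading on day 1 | Day 2 | Day 3 | Days 4–6 |
|---|---|---|---|---|---|
| 48 h | 2.9 | 4% | 36% | 35% | 24% |
| 40 h | 2.6 | 11% | 44% | 28% | 17% |

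On these assumptions 96% and 89% of women would have no movement-pain reading on postoperative day 1. On average the series starts 1.6 to 1.9 days later than the outcome definition requires.

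**Step 2: shift between arms if stay differs by 8 h.** 8/24 = 0.33 day. The simulated means agree: 2.918 − 2.583 = 0.335 day. With pain falling linearly by s mm per day, every reading moves by b = s × 0.33 mm, and so does their average.

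**Step 3: what the shift would do to the test.** Take the time-averaged AUC of the three readings to have the plan's SD of 20 mm. With 190 per arm, SE = 20 × √(2/190) = 2.052 mm.

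- Power for a true 10 mm benefit = Φ((10 − b)/2.052 − 2.132).
- Type I error = 1 − Φ(2.132 − b/2.052) + Φ(−2.132 − b/2.052).

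| Assumed fall (mm/day) | Shift b (mm) | Type I error | Power for a true 10 mm |
|---|---|---|---|
| 0 (timed from surgery) | 0 | 3.3% | 99.7% |
| 3 | 1.0 | 5.4% | 98.8% |
| 5 | 1.7 | 9.5% | 97.3% |
| 10 | 3.3 | 30.6% | 86.8% |
| 15 | 5.0 | 62.0% | 62.0% |

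The type I column supposes that stay differs by 8 h while pain at any given time since surgery does not. If the AUC also includes the PACU and 5 h readings, the shift is diluted.

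**The case against.** The strongest reply is that the outcome definition already times these readings from surgery and mentions a 3-day morphine window beside them. On that view, one sentence in a procedural narrative is loose, and every harm described depends on staff following it. This stands in part. A reader might infer that the trial has chosen to time its pain outcome from discharge; the article shows a contradiction, not such a choice. But the loose sentence is the one that tells staff when to take the reading, and nothing overrides it.

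Three further limits also stand:

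- **Scope.** A reader might infer that all the primary pain data are compromised, or that early pain goes unmeasured. The PACU and 5 h readings are secure under either sentence.
- **The 8 h difference.** It is a power assumption for a secondary outcome, with the arms unlabelled. If stay does not differ on average, the shift between arms goes. The late start and the pain-dependent clock remain.
- **The slope.** The article contains no pain trajectory. A fall of 15 mm per day would mean 30 mm between the first and third readings, in women already judged to have controlled pain. That end of the range is hard to credit.

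The calculation in steps 2 and 3 also covers only one mechanism. It moves two otherwise fixed curves by 8 h. If stay is shorter because pain is controlled sooner, that fixed shift is not the right quantity, and the effect of starting both arms at a similar state of recovery is not quantified here.

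**Conclusion.** The contradiction is certain and needs no assumption: one component of a co-primary outcome has two time origins. With the plan's own stay figures the two schedules differ by about one to two days, and under the Data collection text most women would miss the first postoperative morning. The exact percentages rest on the assumed operating hour and stay distribution.

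The bias between arms is conditional. It requires that the Data collection text is followed, that stay differs (8 h taken from the power statement), and that pain is still falling (3 to 15 mm per day, assumed). The shift is then about 1 to 5 mm against the arm discharged earlier, or 10 to 50% of the 10 mm minimal relevant difference.

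A reader might go on to infer that a real benefit would be masked. The figures do not support that: with 190 per arm, power for a true 10 mm benefit stays at about 87 to 99% for falls of 3 to 10 mm per day, and drops seriously only at 15. Some attenuation and some inflation of the type I error are possible; neither is established.

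**What to change.** Reconcile Data collection and the record sheets with the definition in Primary outcomes. The movement VAS is taken on the mornings of postoperative days 1, 2 and 3 for every woman, on the ward if she is still admitted and at home otherwise. State the morphine registration window from the same origin, so that pain and analgesic use cover the same days. The discharge criteria and pain treatment need no change for this.

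The cost is a wording change and making the VAS sheet available from day 1. It should be done before readings are taken under the other schedule, because a missed day 1 reading cannot be recovered. If some women have already been followed, record the actual date of each reading so that its time since surgery is known.

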### Randomization

Randomization will be performed centrally by The Copenhagen Trial Unit. The allocation sequence will be computer-generated and hidden from the investigators and participants. The allocation ratio will be 1:1 and stratification variables will be parity (0 or more), centers (Roskilde or Herlev) and previous larger pelvic surgery (yes/no).

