### Statistical analyses

The statistical analysis plan will be described in detail and published in “BMC Medical Research Methodology”.

Our primary analyses for all outcomes will be adjusted for the three stratification variables (number of previous births (0 or more), centres (Roskilde or Herlev), and previous larger pelvic surgery (yes/no)). Our secondary analysis for all outcomes will be adjusted for the three stratification variables (see above) and other prognostic variables (history of chronic pelvic pain (yes/no), co-morbidity, enlarging of the abdominal incision to remove uterus (yes/no), multiple adherences or need for other laparoscopic procedures (yes/no). Full analysis will be carried out on both groups, the intention-to-treat population (all randomized participants) and observed cases.

Longitudinal data will be analysed using area under the curve, continuous data will be analysed linear regression, dichotomous data will be analysed using logistic regression, and survival data will be analysed using cox regression. We will perform two sided statistical tests.

We will assess if the thresholds for statistical significance and clinical significance are crossed using the five-point procedure as suggested by Jakobsen et al. [14]. This procedure will include adjustments of thresholds for significance according to the number of primary outcomes (*P*-value threshold 0.033) and number of randomized participants. We will use a Bayes factor threshold for significance of 0.1 based on the prior anticipated intervention effect (see sample size calculation).

We will register if postoperative pathologic examination unexpectedly reveals cancer in a stage indicating further surgery, or if surgery must be converted to open surgery, for other reasons than to remove the uterus. However, we expect such cases to be rare and we will therefore include such participants in the primary analysis. Sensitivity analyses will be performed if the proportion of such cases is larger than expected.

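### Estimated uterine weight is recorded before randomisation but left out of the stratification and both prespecified models, so the operative-time comparison gives up some precision.

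*Protocol article*

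**What the plan says.** **What is measured, and when.** The Participants section excludes women with "ultrasound appraisal of uterus weight > 1000 g". The other exclusions (concomitant prolapse surgery, language, consent) are not measurements. The Interventions section states: "Standard preoperative assessment will be performed together with transvaginal ultrasound estimating the size of the uterus". Table 1 in the Data collection section lists "Baseline variables: height, weight, age, prior operations, chronic pain, parity, estimated weight of uterus, indication for operation, site" and marks that row at enrolment. The same section says "Randomization will be performed in the morning of the operation day". An estimate made at the preoperative assessment is therefore available before allocation.

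**How it is used.** The Randomization section says that the "stratification variables will be parity (0 or more), centers (Roskilde or Herlev) and previous larger pelvic surgery (yes/no"). The Statistical analyses section says "Our primary analyses for all outcomes will be adjusted for the three stratification variables". For the secondary analysis of all outcomes it adds "history of chronic pelvic pain (yes/no), co-morbidity, enlarging of the abdominal incision to remove uterus (yes/no"), together with a yes/no item for adhesions or additional laparoscopic procedures. Estimated uterine weight is in none of these lists, and neither is body mass index (BMI), although height and weight are recorded.

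**The outcome concerned.** Operative time is a secondary outcome. The power section gives 101 min against 90 min, SD 36 min, 190 women per arm, alpha 5% and a power of 81%.

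**The concern.** The article treats uterine size as relevant to how the operation goes. Size sets the limit of suitability for laparoscopy, and a large uterus is the accepted reason for a mini-laparotomy. If size also predicts how long the operation takes, the spread of sizes admitted below 1000 g adds between-patient variation that the planned models leave in the residual. A baseline covariate that predicts the outcome removes part of that variation at almost no cost.

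The plan does reach for size, but through enlargement of the incision. That is a yes/no event decided during surgery, after allocation, by a surgeon who cannot be blinded. The continuous baseline measurement, which allocation cannot influence, is left out.

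The article defers detail to a separate statistical analysis plan. It nevertheless names both covariate sets and applies them to every outcome, so this is a choice the document makes and not one it leaves open.

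At stake is the width of the interval for operative time, the outcome for which the Background and Discussion cite earlier evidence in favour of 3D laparoscopy.

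**Working it through.** **Inputs from the article.** Difference 101 − 90 = 11 min; SD 36 min; 190 per arm; alpha 5% (power section for operative time); two-sided tests (Statistical analyses).

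**Input not in the article.** The partial correlation r of estimated uterine weight with operative time, given the three strata. It is assumed here to lie between 0.2 and 0.5.

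**Step 1: the stated power.**
- SE = 36 × √(2/190) = 3.69 min.
- Power ≈ Φ(11/3.69 − 1.96) = Φ(1.02) = 84.6%. The noncentral t gives 84.4%.
- The article states 81%, so the figure is not reproduced at 5%. At a two-sided alpha of 3.3%, the level used for the primary outcomes, the same formula gives 80.1%, which is close to 81%. That discrepancy is a separate matter; both alphas are carried below so that the conclusion does not depend on it.

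**Step 2: adding the covariate.**
- Residual SD = 36 × √(1 − r²).
- SE = residual SD × √(2/190).
- Half-width of the 95% interval = 1.96 × SE.
- Equivalent number per arm without the covariate = 190/(1 − r²).

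| Assumed r | Residual SD (min) | SE (min) | 95% half-width (min) | Power, alpha 5% | Power, alpha 3.3% | Equivalent n per arm |
|---|---|---|---|---|---|---|
| 0 | 36.0 | 3.69 | 7.2 | 84.6% | 80.1% | 190 |
| 0.2 | 35.3 | 3.62 | 7.1 | 86.0% | 81.8% | 198 |
| 0.3 | 34.3 | 3.52 | 6.9 | 87.7% | 83.9% | 209 |
| 0.4 | 33.0 | 3.39 | 6.6 | 90.1% | 86.8% | 226 |
| 0.5 | 31.2 | 3.20 | 6.3 | 93.0% | 90.4% | 253 |

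The SE falls by 1 − √(1 − r²), which is 2% at r = 0.2 and 13% at r = 0.5.

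**Step 3: what 36 min stands for.** The table takes 36 min as the residual SD of the strata-only model. If the strata already explain some of the variation, that residual SD is below 36 min and the starting power is higher. The proportional fall in the SE is unchanged, because r is a partial correlation, but the gain in power is smaller than shown.

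**Step 4: chance imbalance.** The standard deviation of a standardised baseline difference between arms is √(2/190) = 0.10. One such deviation moves the unadjusted operative-time difference by r × 36 × 0.1026, which is 1.1 min at r = 0.3 and 1.8 min at r = 0.5. Both lie within the SE of 3.69 min, which already includes this source of variation.

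**The case against.** The strongest case against is that nothing in the plan is wrong here. Adjusting for exactly the factors used in stratification is coherent, gives a valid interval and treats all outcomes alike. Operative time is secondary, its power is above 80% on the stated inputs, and no primary outcome or sample size changes. No correlation is given, and at r = 0.2 the gain is slight: 86.0% against 84.6%, and about 0.1 min off the half-width. Other baseline variables, such as age or indication, could be proposed on similar grounds.

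Most of this stands and limits the point to an improvement in precision. It does not remove the point: the variable is already collected, it precedes allocation, and the plan itself tries to account for size through a worse measure.

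Three stronger readings are tempting, and the documents do not support them.

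- A reader might infer that operative time is compared with no adjustment. Both models adjust for the three strata, and the secondary model adds further covariates. Only uterine size itself is missing.
- A reader might infer that the comparison is biased, or that chance imbalance in size is a further, uncorrected harm. Randomisation keeps the comparison unbiased in expectation, and Step 4 shows that imbalance is part of the SE, so listing it separately counts the same loss twice.
- A reader might put BMI on the same footing as uterine weight. The Background mentions "the requirement of advanced laparoscopic skills, and challenges in especially obese patients" among reasons for the slow uptake of laparoscopy, separately from operating length. That is weaker support, and the undefined co-morbidity covariate might capture part of it.

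**Conclusion.** The point holds as a modest loss of efficiency in one secondary outcome. Estimated uterine weight is a pre-randomisation measurement and the only numeric eligibility limit, yet it is absent from the stratification and from both models, where a post-randomisation stand-in takes its place in the secondary analysis. The comparison remains valid.

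The size of the loss rests entirely on an assumed correlation. It is negligible near r = 0.2 and becomes material at about r = 0.4, where adjustment is worth some 36 extra women per arm (226 − 190). The direction is the same at alpha 5% and 3.3%. Nothing in the documents shows how strongly size below 1000 g drives operating time, so the upper end of the range should not be quoted as the expected gain.

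**What to change.** For operative time, prespecify baseline estimated uterine weight as a continuous covariate in the primary model, alongside the three stratification variables. State that the value is the ultrasound estimate recorded at enrolment and not the specimen weight obtained after removal. Baseline BMI may be added as an option. Keep the strata-only model as a supporting analysis. The stratification need not change.

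The covariate should be named before outcome data are seen, because adding it afterwards would look data-driven.

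The cost is one line in the analysis section, one or two model degrees of freedom with 380 women, and a primary model for this outcome that differs from the uniform model used elsewhere. No new data are needed.
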